## Ethical considerations

5

The study may involve individuals at risk of harming themselves and/or others. Furthermore, it is possible that on some occasions, social media posts draw negative publicity, and some participants might feel distressed and/or upset as a result. To mitigate these risks, we will take the following precautions:

The project will be explained to the participants, and their written and oral informed consent will be obtained. The research staff are fluent in English, Urdu and other local languages of the study sites. They will ensure that the participants are aware of the requirements for taking part in the study and the social media campaign. The participants may withdraw from the study at any time, and any social media posts and/or data they provided will be excluded from the study.

There will be a dedicated Photovoice facilitator managing the communication, Photovoice process and safety of the participants throughout the Photovoice process. Facilitators will call participants on a fortnightly basis to check whether there are any safety-related, personal or logistical difficulties with taking pictures and whether the participants need additional support. In case a participant discloses unpleasant experiences while taking pictures and/or if they mention remembering unpleasant memories about their past accident(s) resulting in burn injuries, the Photovoice facilitator will discuss these with their clinical supervisors; the clinical supervisor from the team will then call the participant to follow up on the issue. The participant will be signposted for further psychological help if needed.

In case a participant discloses thoughts of harming oneself and/or others during the Photovoice workshops and/or on social media platforms, a distress protocol will be used, and it will be individualised for each participant. At the introductory workshops, the participants will be asked to provide the names and contact details of three relatives/friends. If a participant discloses thoughts of harming oneself and/or others at any point, the psychologist from the research team will perform a risk assessment (see exploring risk questions), either in person and/or through a phone call. If deemed necessary, the psychologist will contact the relatives of the participant and take them to a nearby psychiatric unit in a public hospital. As a last resort, hospital emergency services will be contacted if the participants and/or their relatives cannot be reached. In case of an adverse event (i.e., suicide attempt or self-harm), an Adverse Event Form will be completed and sent to the principal investigator within 24 h of reporting the event. Furthermore, if the individual discloses thoughts of self-harm and/or harming others and is a social media follower unknown personally to the research staff, the latter will send a private message with emergency contact numbers and support resources.

Participants may share their photos with the Photovoice facilitators before the photo reflection workshops or prior to the closed and/or open exhibitions. This would be necessary to avoid inconveniences and delays due to the postal system in Pakistan. To protect the participants’ privacy and confidentiality, the authors will provide the participants and the research assistants with mobile phones and will communicate exclusively through these phones (not through their personal mobile phones). The participants’ pictures will be stored on the research assistants’ mobile phones and will be permanently deleted as soon as these are transferred to the data management system at the Pakistan Institute of Living and Learning. The data management system is protected with a username and password, and it is only accessible to the research staff in Pakistan.

A moderation process will be implemented to ensure the safety of the participants throughout the social media campaign. The research staff will manage the social media accounts of the project and will actively monitor comments and respond to posts. Offensive or harmful comments will be deleted, and any users engaging in harassment, will be blocked. If a negative exchange between the participants and followers of the social media accounts occurs about particular photos and/or stories, the psychologist of the research team will contact the participant via telephone and/or email and will assess their psychological distress. If deemed necessary, the participant will be signposted to the available psychological support services in their area.

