### Research design

2.1

This study is a cohort study with three measurement points conducted at 6- to 12-month intervals (*n* = 600). The impact of the health communication campaign will be evaluated by measuring indicators of knowledge, attitudes and practices related to burn first aid, as well as psychological variables and health information-seeking variables, among the following groups: the exposure group (i.e., burn survivors [*n* = 200] and caregivers [*n* = 100] exposed to campaign messages), the non-exposure group (i.e., burn survivors [*n* = 250] not exposed to campaign messages) and the Photovoice group (i.e., burn survivors [*n* = 50] who participate in Photovoice and are exposed to the campaign messages). Figure 1 presents the campaign process and the planned activities in different phases.

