##### Sampling

2.3.1.1

To investigate the preliminary effects of Photovoice on the primary and secondary outcomes of interest, we will categorise participants into three groups, as described previously (see Figure 1). As this is only a pilot study and the objective is mostly to co-adapt the Photovoice programme and evaluate its potential in building capacity for a larger evaluation, no sample size calculation has been deemed appropriate (48, 49). This study will also help us determine whether we can maintain an acceptable attrition rate of Photovoice for a future RCT (50). An effective sample size for this study was determined based on the sample size of previous exploratory studies using Photovoice (31).

Consenting baseline participants will be invited to attend the introductory Photovoice workshop via email and/or a telephone call. The invitation letters will be sent via email and/or postal mail. One-to-one meetings will be organised with those who do not want to be in a group setting.

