## Data analysis plan

4

To compare changes in self-reported outcomes within groups across two time points (see Table 1) in the sample (*N* = 600), we will implement linear mixed-effects models implemented in R (R version 3.6.1) (51) using the lme4 package and in SAS 9.4. This method considers correlations within participants, allowing them to be modelled appropriately. It also estimates within-subject variability, in addition to estimating model parameters. The method can handle and model missing outcome data under the assumption that the data are missing at random. The mixed model uses a longitudinal data structure that includes both fixed and random effects, and baseline measurement is usually included as a covariate. Time will be included in the model as an interacting categorical variable to observe any time-varying trends. Cohen’s *d* for the effect of Photovoice will be calculated as the difference between baseline-corrected estimated means divided by the pooled standard deviation. A two-sided *p* < 0.05 indicates statistical significance. In addition, demographic variables, such as age, education, gender, marital status, geographic location (i.e., rural vs. urban residence) and household situation (i.e., living with a single and/or an extended family) will be included in the linear mixed models to test for potential moderating and mediating effects on behavioural intention related to burn prevention and first-aid practices. A stepwise selection of the variables will be conducted to determine which variables to keep in the model. As we add the variables, we will immediately eliminate those that do not reduce the Akaike information criterion (AIC) by using the *stepAIC* R function from the library *MASS*. If two or more independent variables in a model are found to be strongly correlated, a variance inflation estimate of less than 5 will be used to determine whether collinearity is present. If the relationship is found to be non-linear, attempts will be made to model the outcome data via the use of splines or polynomials in the *nlme* package in R. The normality of residuals will be assessed graphically using histograms and Q-Q plots. Detailed statistical analyses following Good Clinical Practice: Consolidated Guidelines ICH E9 (52) and Medical Research Council guidelines for developing complex interventions (53) will be described in the statistical analysis plan, which will be finalised before the data lock stage.

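### The withdrawal rule excludes questionnaires already completed, which conflicts with the missing-at-random mixed model planned on N = 600

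*Protocol article*

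**What the plan says.** Section 5 (Ethical considerations) lets participants leave whenever they wish and states that, if they do, "any social media posts and/or data they provided will be excluded from the study". Posts are named separately from data, and no exception is made for questionnaires completed before withdrawal.

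Section 4 (Data analysis plan) compares changes in self-reported outcomes in the sample of N = 600 with linear mixed-effects models. On missing outcomes it says: "The method can handle and model missing outcome data under the assumption that the data are missing at random". It adds that "baseline measurement is usually included as a covariate", and it defines the Photovoice effect as a Cohen's d built on baseline-corrected estimated means.

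Section 2.3.1.1 (Sampling, under Photovoice) gives the pilot a retention aim: "This study will also help us determine whether we can maintain an acceptable attrition rate of Photovoice for a future RCT". Section 2.1 sets that group at 50: "burn survivors [*n* = 50] who participate in Photovoice and are exposed to the campaign messages". The sample size paragraph at the end of section 2.2.5 requires 478 participants and recruits 600 to allow for 20% dropout. The text does not separate formal withdrawal from loss to follow-up.

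**The concern.** A likelihood-based mixed model is valid under missing at random because the scores seen before someone leaves carry information about the scores not seen. If those earlier scores are removed, the model has nothing to work with for that person, and the analysis becomes one of people who did not withdraw. It is then no longer an analysis of all 600.

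This matters only if withdrawal is related to outcome or group, which is plausible here. Section 5 itself foresees negative publicity and distress from social media posts, and self-stigma and social interaction anxiety are measured outcomes. Photovoice participants alone go through reflection workshops and exhibitions, with a questionnaire after each. They have more occasions to withdraw, more data to lose, and a group of only 50 in which a few deletions count.

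Deletion also removes the means of describing who left. The pilot wants to judge whether Photovoice attrition is acceptable, and that judgement is better informed if withdrawers can be compared with stayers on baseline and interim scores.

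**Working it through.** **1. The plan's own figures.** Required 478, dropout 20%: 478 / 0.80 = 597.5, rounded up to 598, against 600 stated. Conversely 600 × 0.80 = 480, which is at least 478. The dropout allowance reproduces, and the withdrawal rule does not change it.

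**2. How many records the rule could remove.** Planned loss is 600 × 0.20 = 120, or 50 × 0.20 = 10 in Photovoice if the same rate applies there. The share of losses that are formal withdrawals is not given, so it is shown as a range:

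| Share of losses that withdraw | Of 600 | Of 50 in Photovoice |
|---|---|---|
| 0% | 0 | 0 |
| 25% | 30 | 2.5 |
| 50% | 60 | 5 |
| 100% | 120 | 10 |

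**3. Keeping versus deleting earlier data, within one group.** This is a large-sample simulation of 200,000 records with three visits. Assumptions, none from the documents: SD 1, within-person correlation 0.6, true means 0, 0.30 and 0.50, and dropout more likely after a low last observed score (logistic slope 0, 0.7 or 1.5 per SD). Every dropout is treated as a withdrawer, so the 100% row above applies. Keeping means a likelihood estimate from all observed scores; deleting means every dropout's record is removed.

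| Dropout | Slope | Kept: t2 mean | Kept: change | Deleted: baseline mean | Deleted: t2 mean | Deleted: change |
|---|---|---|---|---|---|---|
| 20% | 0 | 0.50 | 0.50 | 0.00 | 0.50 | 0.50 |
| 20% | 0.7 | 0.50 | 0.50 | 0.11 | 0.58 | 0.47 |
| 20% | 1.5 | 0.51 | 0.50 | 0.20 | 0.65 | 0.45 |
| 35% | 0.7 | 0.50 | 0.49 | 0.20 | 0.64 | 0.44 |
| 35% | 1.5 | 0.50 | 0.50 | 0.34 | 0.75 | 0.42 |

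At 20%, deletion moves the t2 mean by about +0.08 to +0.15 SD and the change by about −0.03 to −0.05 SD. Keeping the data leaves essentially no bias. With dropout completely at random (slope 0) the two agree.

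**4. The Photovoice contrast.** Assume 15% withdraw from Photovoice and 5% from the exposed group, with withdrawers 0.5 SD below stayers. Deleting a fraction w shifts a raw mean by 0.5 × w, so the raw contrast shifts by 0.5 × 0.15 − 0.5 × 0.05 = 0.075 − 0.025 = 0.05 SD. The plan, however, uses baseline-corrected means. Simulating the same inputs with correlation 0.6:

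- Withdrawal driven by the baseline score: the baseline-adjusted contrast moves by 0.00 at t1 and t2; the unadjusted change moves by −0.02 SD, against Photovoice.
- Withdrawal driven by the t1 score: the adjusted contrast moves by about 0.03 to 0.035 SD at t1 and about 0.01 SD at t2, in favour of Photovoice.

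The reason is that, with baseline as a covariate, someone who has only a baseline score contributes no outcome row, so deleting that record changes nothing in the contrast. The loss bites for those who already have t1 data.

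**5. Attrition count.** If 10 of 50 leave Photovoice, attrition is 20% (exact 95% CI 10% to 34%). This needs only the enrolment and withdrawal logs.

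**The case against.** The rule sits among ethical safeguards and is chiefly aimed at publicly shown photos and stories. The study has approval from two ethics committees, and whether questionnaires may be kept depends on consent wording that is not shown. Analysis sets are commonly left to the statistical analysis plan, to which section 4 defers the detail. The effect on the planned contrast is at most a few hundredths of an SD, small beside the imprecision of a 50-person pilot group.

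The points on consent and size stand, and they limit how serious this is. The deferral does not settle it: the exclusion is a stated rule, and an analysis plan cannot restore data that the protocol says are excluded.

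Three stronger readings are tempting and are not supported.

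- A reader might infer that the rule defeats the mixed model altogether. It does not: the text does not apply the rule to people who miss a visit or are lost without withdrawing. Their scores remain and missing at random can be used for them as planned.
- A reader might infer that Photovoice attrition is hidden. The rule excludes data that participants provided, not the fact that they enrolled or left. Facilitators follow five participants each, a CONSORT diagram is referred to, and nothing takes withdrawers out of the denominator.
- A reader might take 0.05 SD in favour of Photovoice as the bias. That is a shift in raw means; the planned estimate is baseline-corrected, and neither that size nor that direction carries over generally.

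**Conclusion.** The conflict between sections 5 and 4 is real and needs reconciling. For formal withdrawers, and chiefly those with t1 data, the analysis conditions on not having withdrawn.

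The likely bias is modest and its direction uncertain. Under the assumptions shown, it is about 0.03 to 0.05 SD in within-group change if the whole 20% loss is formal withdrawal related to earlier scores, and zero to a few hundredths of an SD in the baseline-corrected Photovoice contrast. It is nil if withdrawal is unrelated to outcome and group. These sizes rest on an assumed correlation, dropout mechanism and withdrawal share, none of which the documents give.

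The other loss is descriptive: withdrawers cannot be set against stayers on earlier scores. This is a cheap improvement rather than a threat to the study's main conclusions.

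**What to change.** Reconcile the two sections. In section 5, state that questionnaire data collected before withdrawal are retained and analysed unless the participant asks for their deletion, and that photos and social media posts are removed on withdrawal. Distinguish withdrawal of consent from loss to follow-up, and record the date of withdrawal and any reason offered. In section 4, say that the mixed model uses all retained scores, and report withdrawals (and any deletion requests) by group with everyone enrolled as the denominator.

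The cost is one sentence in the protocol, information sheet and consent form, with ethics notification. People who consented under the present wording keep their right to deletion, so the change may not reach all participants in a study scheduled to start in March 2024. No change to the sample size is needed.

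### The adverse event definition covers only suicide attempt and self-harm, so the other harms the protocol anticipates are managed but not counted as adverse events

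*Protocol article*

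**What the plan says.** The only definition of an adverse event in the article is in section 5: "In case of an adverse event (i.e., suicide attempt or self-harm), an Adverse Event Form will be completed and sent to the principal investigator", with the time limit "within 24 h of reporting the event". The form and the report to the principal investigator are attached to nothing else.

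The same section sets out a wider list of risks. It opens with "The study may involve individuals at risk of harming themselves and/or others" and adds that it is possible that "social media posts draw negative publicity, and some participants might feel distressed and/or upset as a result". It then gives a response for each kind of problem:

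- If a participant reports unpleasant experiences or memories while taking pictures, "the Photovoice facilitator will discuss these with their clinical supervisors; the clinical supervisor from the team will then call the participant to follow up".
- If a participant discloses thoughts of harm to self or others, "a distress protocol will be used, and it will be individualised for each participant". A psychologist assesses risk, and the escalation can reach relatives, a psychiatric unit or hospital emergency services.
- After a negative online exchange involving a participant, the psychologist "will contact the participant via telephone and/or email and will assess their psychological distress". Harmful comments are removed and harassing users are blocked.

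Section 2.3.1.1 describes the Photovoice component as a pilot building towards a larger evaluation and a future RCT. Section 2.1 puts 50 burn survivors in that group.

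**The concern.** The risks the section expects and the events it records do not match. The narrow bracket leaves out everything except the two rarest and most severe outcomes. Harm actually done to others is outside it, although the section's first sentence names that risk. So is a disclosure serious enough to end in referral to a psychiatric unit, unless an attempt or self-harm also took place.

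This is not a detail left for the statistical analysis plan. The article chose to define the term, and an analysis plan can tabulate only what the forms collect. A pilot intended to inform a future RCT should be able to say how often its own foreseeable harms occurred. If the definition is applied as written, the count of adverse events will not answer that, and no other count is described. Events not captured at the time are hard to reconstruct afterwards.

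**Working it through.** No figure in the plan is at issue, so the main check sets the parts of section 5 side by side.

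| Anticipated harm | Stated response | Adverse Event Form? | Count stated? |
|---|---|---|---|
| Suicide attempt or self-harm | Form to the principal investigator | Yes | Not stated |
| Disclosed thoughts of harm to self or others | Distress protocol, risk assessment, possible escalation | No | No |
| Harm actually done to others | None specific to the act itself | No | No |
| Unpleasant experiences or memories | Supervisor discussion and call, signposting if needed | No | No |
| Negative exchange about a participant's photo or story | Psychologist contact, signposting if needed | No | No |
| Harassment by users | Comments deleted, users blocked | No | No |

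**Do other records fill the gap?** Only in part.

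- Field notes, transcripts and social media comments (section 4) are analysed thematically, not as events.
- Harmful comments are deleted under section 5, and no step to log them first is described.
- Data from participants who withdraw are excluded (section 5), so someone who left because of distress could drop out of the results.
- The scales in Table 1 are taken at a few time points and identify neither an event nor its cause.

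**Illustration of size.** The one input from the document is n = 50 (section 2.1). All rates are assumptions.

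Chance of no recorded adverse event = (1 − p)^50, where p is the rate of suicide attempt or self-harm:

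- p = 0.5%: 0.995^50 = 0.778, or 78%
- p = 1%: 0.99^50 = 0.605, or 61%
- p = 2%: 0.98^50 = 0.364, or 36%

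Expected number of participants with distress or re-experiencing = 50 × q:

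- q = 10%: 5
- q = 20%: 10
- q = 30%: 15

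None of these would be an adverse event under the definition as written. If the pilot recorded 0 of 50, the one-sided 95% upper bound would be 1 − 0.05^(1/50) = 5.8%. That bound would apply to suicide attempt or self-harm only and would say nothing about the other harms in the table.

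**The case against.** The strongest reply is that the bracket may not be a closed definition. The article uses *i.e.* loosely. In section 2.3.2.4 it introduces power sharing as what is evidently an example of an ethical challenge, and key stakeholders are glossed differently in sections 2.2.1, 2.2.3 and 2.3.2.4. This has some force. But the article also uses *e.g.* for examples (sections 2.3.2.4 and 4) and *i.e.* for exact definitions (the study groups in section 2.1). If examples were meant, the sentence still needs correcting, because staff will apply it as it stands.

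A reader might infer that these harms are never recorded at all. The article does not say that. It is silent on how supervisor calls, distress-protocol uses and psychologist contacts are logged. It provides weekly clinical supervision and a toolkit with distress and debriefing policies, and the full protocol, the form and the distress protocol are not shown.

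A reader might also infer that the pilot is bound to report almost no harm. That presumes a harms-reporting rule, and the article states none.

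The time limit could be read as leaving the delay before a report unlimited. It can equally mean 24 h from the moment the event is reported to staff, so it is ambiguous rather than wrong.

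Two further cautions stand. Identification without consent is not among the risks named in section 5 and triggers no contact there, so it is not part of this mismatch. And Photovoice asks people to depict their burn experience, so some painful recall is expected. Treating each such mention as an adverse event with a 24 h report would be excessive.

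**Conclusion.** The point holds in a limited form. As written, section 5 restricts adverse events to suicide attempt and self-harm. The other harms it anticipates are managed but not recorded as adverse events, and no route for counting them is stated. This rests on the plain wording of the bracket and on the absence, in the article, of any other link to the form.

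The documents do not support saying that the harms go wholly unrecorded or that a near-zero harm report is guaranteed. The 36% to 78% range depends entirely on assumed rates of 2% to 0.5% and shows only how uninformative the narrow count could be in 50 people.

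No primary outcome, sample size or planned model is affected, and almost every named risk has a response. It is a moderate point, not one that must be fixed before the study can be relied on.

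**What to change.** Reconcile the definition in section 5 with the risks listed there:

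1. State that suicide attempt, self-harm and actual harm to others are adverse events.
2. State that each distress-protocol use, risk assessment, supervisor or psychologist contact, signposting and harassment episode involving a participant is logged as a safety event. Expedited reporting need not apply to all of these.
3. Say that the 24 h runs from when staff become aware of the event.
4. Report events by type, descriptively for the Photovoice group. The fortnightly safety calls (sections 2.3.2.1 and 5) are described only for that group, so detection differs and counts are not comparable across groups. The report should say so.

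The cost is a few sentences in the protocol, more forms and a higher reported event count. Most of these episodes already trigger a staff action, so the added work is mainly the record. The change concerns recording only and alters no clinical management.

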##### Self-Stigma Scale (SSS)

2.2.5.2

The SSS (35) has both long (39 items) and short (9 items) versions, comprising three self-stigma subscales (cognitive, affective and behavioural), and is used to assess internalised stigma. In this scale, respondents rate their levels of agreement with each item (e.g., ‘My identity as a ______is a burden to me’ [cognitive], ‘I fear that others would know that I am a_____’ [affective], and ‘I estrange myself from others because I am a____’ [behavioural]) on a four-point Likert-type scale (1 = strongly agree to 4 = strongly disagree). The blank spaces on the scale were filled with ‘mental health consumer’ when used in a sample of mental health consumers and with ‘recent migrant’ when used in a sample of migrants (35). In this study, the blank spaces will be filled with the term ‘burn survivor’ to measure internalised stigma associated with this identity. Higher scores indicate greater self-stigma. Internal consistency estimates ranged from 0.87 to 0.91 for the total scale and from 0.80 (behavioural) to 0.84 (affective) for the subscales (29). Mean scores between 2.40 (SD = 0.66) and 2.41 (SD = 0.60) reflect moderate to high internalised stigma (35). More recently, the reliability of a shorter version of the scale (5 items) has been established, with Cronbach’s alphas of 0.93 and 0.91; it has demonstrated adequate convergent and criterion-related validity in an English-speaking sample in the US (36).

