In line with the flexibility of the Photovoice approach as a participatory action research method, we decided to follow reflexive thematic analysis based on Braun and Clarke’s six-phase approach (54), with NVivo software supporting data management and coding. All reflection sessions and exhibitions will be audio-recorded, transcribed verbatim and pseudonymised. Two researchers will independently code a subset of transcripts to enhance rigour and then collaboratively develop an analytical framework. Both inductive and deductive coding will identify emergent themes. Thematic analysis will be conducted on captions, participant narratives and social media comments. Special attention will be given to potential group differences (e.g., male vs. female participants, urban vs. rural residence, severity of burn injuries, and communication or health literacy differences). Data analysis will occur in parallel with data collection. Thick descriptions of the context of each workshop and the interactions with each participant will be documented in field notes. The team will agree when data saturation has been reached.

Social media metrics and textual analysis of photo captions and viewer comments will be employed to determine audience reach and engagement. These metrics will also provide insights into perceptions, knowledge and attitudes related to burn survivors and their experiences. The analytics dashboards provided by each social platform will be used to gather key metrics. The main metrics include likes, comments, shares and emojis. Specifically, the comments will be used for thematic analysis to extract more narratives, stories and lived experiences. Overall, a triangulation approach will be used to integrate the results from the different data sources, provide a comprehensive overview of the findings and enhance confidence in the conclusions (55).

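### Project staff delete hostile comments that are also data on attitudes to burn survivors, and no copy before deletion is described

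*Protocol article*

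**What the plan says.** Two parts of the Protocol article bear on the same material.

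**Moderation (section 5, Ethical considerations).** The project's own staff run the accounts: "The research staff will manage the social media accounts of the project and will actively monitor comments and respond to posts". The rule for hostile content is: "Offensive or harmful comments will be deleted, and any users engaging in harassment, will be blocked". Section 2.4 also mentions a moderation procedure carried out by the research assistants, without further detail.

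**Analysis (section 4, Data analysis plan).** Comments are a source for the qualitative work: "Thematic analysis will be conducted on captions, participant narratives and social media comments". They are also part of the campaign metrics: "Social media metrics and textual analysis of photo captions and viewer comments will be employed to determine audience reach and engagement". Comment counts are among the main metrics taken from the platform dashboards. The article then says what is to be learned: "These metrics will also provide insights into perceptions, knowledge and attitudes related to burn survivors and their experiences". The results are to be triangulated with the other data sources.

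The article does not say that a comment is saved, logged or counted before removal. It also does not say whether removed comments enter the analysis.

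**The concern.** The team that analyses the comments also removes some of them, and the ground for removal is hostility. Hostility is part of what the analysis is meant to show when it describes how viewers perceive burn survivors. If no copy is kept, the analysed set is selected on the attitude under study.

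This source is supplementary, but nothing else in the plan replaces it. Table 1 gives the Knowledge, Attitudes and Practice Scale to survivors and family members, and the campaign effectiveness measure to those two groups plus health care professionals and key informants. No listed instrument samples the wider online audience, which section 2.4 expects to be about 5 million people. The comments and metrics are the only described evidence on how that audience responds. A reading of them that leans favourable would pass through the triangulation into the overall conclusions, and no count of deletions or blocks is described that would let a reader judge how much was removed.

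**Working it through.** The plan states no figure on this point, so there is nothing to reproduce. The check sets the provisions side by side and then illustrates the direction of the bias with assumed values.

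**Step 1. Who removes, and what.** Research staff delete offensive or harmful comments and block users who harass (section 5). Comments that are critical but neither offensive nor harmful may stay.

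**Step 2. What is analysed.** Social media comments, by thematic analysis, textual analysis and counts, with perceptions of and attitudes to burn survivors among the stated yields (section 4).

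**Step 3. Is there a capture step between the two?** None is described in section 2.4, 4 or 5. Section 4 says that analysis runs in parallel with data collection. That makes capture before deletion possible but does not state it, since a moderator may remove a comment before anyone has coded it.

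**Step 4. What is not touched.** Stigma as an outcome is measured by the Self-Stigma Scale, completed by survivors at t0, t1 and t2 (Table 1; section 2.2.5.2) and used "to measure internalised stigma associated with this identity". Deleting a public comment edits none of those responses, and the same holds for the other questionnaires. On harms, the article says: "In case of an adverse event (i.e., suicide attempt or self-harm), an Adverse Event Form will be completed". Hostile comments are not a listed event, so moderation takes nothing out of that record.

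**Step 5. Direction of the bias (illustration only).** Let h be the true share of hostile comments and m the fraction of those deleted without a copy. Both are assumptions; the article gives neither. Per unit of comments, h(1 − m) hostile comments remain out of a total of 1 − hm, so

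visible hostile share = h(1 − m) / (1 − hm).

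| h | m = 50% | m = 80% | m = 100% |
|---|---|---|---|
| 5% | 0.025/0.975 = 2.6% | 0.010/0.960 = 1.0% | 0% |
| 10% | 0.050/0.950 = 5.3% | 0.020/0.920 = 2.2% | 0% |
| 20% | 0.100/0.900 = 11.1% | 0.040/0.840 = 4.8% | 0% |

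Whenever h lies strictly between 0 and 1 and m is above 0, the visible share is below h. The table shows only that the error runs one way. It says nothing about the size to expect in this study.

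**The case against.** The strongest reply is that this rests on silence in a condensed article. Removing a comment from a public page does not remove it from the research data. The moderation procedure and the social media guidelines in the Photovoice toolkit (section 2.3.2.4) may well include an export, and operational detail of that kind often sits in a fuller document. This stands in part: the article does not say that deleted comments are lost or excluded, and that they are is an inference. It does not dispose of the point, because two stated rules work against each other. Elsewhere the article does describe transfer before deletion: in section 5, participants' photos are erased from staff phones only once they are in the data management system. For comments it states deletion alone.

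A second reply is that the stated purpose of the metrics is reach and engagement, and that the comments are mainly to supply narratives and lived experiences. That limits the weight of the point. The article nevertheless adds perceptions and attitudes as something the material will show, and that use is exposed.

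Several stronger readings are tempting and are not supported:

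- **That the stigma result is biased.** The stigma outcome is a survivor questionnaire; no stigma outcome is defined from comments.
- **That harms are removed from the safety record.** Hostile comments were never part of the adverse event record.
- **That blocking would create a false improvement over time.** Blocked users would drop out of later comments, but the plan contains no analysis of comment tone over time.
- **That section 5 contradicts itself on protection.** It names negative publicity as a risk and has the psychologist contact the participant in the case described as "If a negative exchange between the participants and followers of the social media accounts occurs about particular photos and/or stories". A gap appears only if a one-way hostile comment is held not to be an exchange, and the article does not define the word so narrowly. The contact rule needs no change on this ground.

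**Conclusion.** The point holds as a limited one. Applied as written, moderation selects the comment data towards favourable reactions, and the study would be unable to report how often hostile comments occurred or how many users were blocked. The affected result is the supplementary, comment-based reading of public attitudes, together with the comment counts so far as deleted comments drop out of them. No primary or secondary questionnaire outcome is affected.

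The conclusion assumes that at least some comments are deleted and that no copy is kept first. The article is silent on the second condition; if copies are already archived and coded, the bias disappears and only a sentence saying so is needed. The size cannot be derived from the documents. Moderation protects participants and should not be weakened; what is missing is a described record of what it removes. This is a cheap improvement rather than a flaw that threatens the main results.

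**What to change.** In section 5 (Ethical considerations), state that before a comment is deleted or a user blocked, the moderator saves a pseudonymised, time-stamped copy of the comment, with the reason for removal, to the project data system.

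In section 4 (Data analysis plan), state that the archived comments are included in the thematic analysis, and that the numbers of deleted comments and blocked users are reported alongside the engagement metrics.

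Moving a comment off the public page can stay as prompt as now, so participant protection is unchanged. The cost is two sentences, a few seconds per deleted comment for staff who already read and remove them, and secure storage of offensive text. The log should be in place before the campaign starts, because a comment deleted without a copy may not be recoverable.
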